### Secondary outcomes

The secondary objectives are to determine if the intervention is superior to standard-of-care, by evaluating:
The HRQoL at three months after hospital discharge.The incidence of chronic pain and the degree of functional limitation at 3 and 6 months after hospital discharge.The incidence of anxiety and depression at 3 and 6 months after hospital discharge.The incidence of post-traumatic stress syndrome at 3 and 6 months after hospital discharge.

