#### Baseline visit

The baseline visit will take place between 4 to 6 weeks after hospital discharge. Information regarding the study will be given to the patient, and informed consent will be obtained. After that, the patient will be randomized. During this first visit, demographic data, medical history, and ICU and hospitalization variables will be collected from all the included patients, regardless of their randomization arm. All patients will complete a series of questionnaires to evaluate their quality of life and the presence of anxiety, depression, or post-traumatic stress disorder. The presence of pain and its influence on the patients’ lifes will also be evaluated.

Intervention group

The intervention consists of a program that includes early patient care, therapeutic education, and psychological intervention. It will be implemented across three medical visits scheduled as follows:
Visit 1 Intervention group, 4 to 6 weeks after hospital discharge.Visit 2 Intervention group, 8 weeks after hospital discharge.Visit 3 Intervention group, 18 weeks after hospital discharge.

Components:
Interview and physical examination.Therapeutic education about the PICS, orally and in writing with specific documents delivered at the end of the visit, i.e., a PICS fact-sheet developed by the investigators and a rehabilitation manual recommended by the Follow-up and Rehabilitation Committee of the Argentine Society of Intensive Care, SATI [14].Therapeutic education about pain (if the patient reports pain) which includes an explanation of pain neurophysiology, the rational use of drugs prescribed by other specialists, information about how to manage daily life activities, and the importance of pre-emptive pain management for proper rehabilitation.

A psychological intervention will be conducted if the following criterium is met: a score higher than 8 on the hospital anxiety and depression (HAD) test depression subscale (supplement, questionnaire Q1) [17]. The intervention protocol will consist of 7 weekly sessions lasting one and a half hours each (supplement, Table 1). The intervention in depression is based on Rehm’s model of self-control. Psychological interventions may cause adverse events resulting in worsening of patients’ clinical course (overdose, self-harm, and self-harm attempts). Therefore, the investigators will monitor any related symptom, report it as an adverse event, and refer the patient for treatment by a specialist unit.

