The impact of the intervention program on the incidence of anxiety or depression will be assessed by the Hospital Anxiety and Depression test (HAD) (supplement, questionnaire Q1) [17], consisting of 14 questions, with two subscales, one for anxiety and the other for depression, with seven items each and a maximum score of 21 for each subscale. The cut-off points are as follows: 0 to 7 imply the absence of clinically relevant anxiety and depression, 8 to 10 imply de presence of symptoms that require consideration, and 11 to 21 it report the presence of relevant symptoms, with a very probable diagnosis of anxiety or depression. According to Bjelland’s review, cut-off points equal or greater that 8 will be used as abnormal anxiety or depression’s values. This test will be performed at the baseline visit and at 3 and 6 months [25].

Finally, the incidence of post-traumatic stress disorder (PTSD) [26] will be evaluated with the post-traumatic stress disorder checklist questionnaire (PCL-5) [27]. It contains 20 questions that correspond to the DSM-V criteria. Participants will rate their symptoms on a scale of 0 (not at all), 1 (slightly), 2 (moderately), 3 (quite) to 4 (extremely), with a score ranging from 0 to 80. The overall severity of the symptoms can be assessed adding up the scores of each question (interval 0–80). The severity of each symptom can also be evaluated adding up the scores of the questions. DSM-5 symptom cluster severity scores can be obtained by adding up the scores for the items within a given cluster, i.e., cluster B (items 1–5), cluster C (items 6–7), cluster D (items 8–14), and cluster E (items 15–20). A provisional PTSD diagnosis can be made by treating each item rated 2 (“moderately”) or higher as a symptom endorsed, then following the DSM-5 diagnostic rule which requires at least: 1 B item (questions 1–5), 1 C item (questions 6–7), 2 D items (questions 8–14), and 2 E items (questions 15–20) (supplement, questionnaire Q6).

For this analysis, questionnaire licensing was obtained. The validated version in Spanish was used for each of them, except for PCL-5 which, being a new questionnaire, is not yet validated in Spanish, but it has the advantage of screening PTSD according to the DSM-V criteria. The questionnaires are shown in the supplement.

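### Anxiety and depression are tested as case or non-case at HAD 8 or more, although full scores are collected at baseline and follow-up; the baseline-adjusted score is the better test, with a gain that depends on who benefits.

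*Protocol article*

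**What the plan says.** Secondary outcomes in the protocol article lists "The incidence of anxiety and depression at 3 and 6 months after hospital discharge". Outcome measurements describes each HAD subscale as having a range up to 21 ("with seven items each and a maximum score of 21 for each subscale") and fixes what counts as a case: "cut-off points equal or greater that 8 will be used as abnormal anxiety or depression’s values". On timing it says "This test will be performed at the baseline visit and at 3 and 6 months". No outcome on the HAD score or its change is named.

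Baseline visit makes psychological therapy conditional on "a score higher than 8 on the hospital anxiety and depression (HAD) test depression subscale". Therapeutic education on post-intensive care syndrome goes to the whole intervention group.

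For PTSD the named outcome is again incidence: "The incidence of post-traumatic stress syndrome at 3 and 6 months after hospital discharge". The case rule differs in kind: "A provisional PTSD diagnosis can be made by treating each item rated 2 (“moderately”) or higher as a symptom endorsed", followed by a minimum number of endorsed items per symptom cluster. The same section says that a 0 to 80 severity total and cluster scores can be obtained.

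Data analysis lists t or Mann-Whitney tests for continuous variables and chi-square or exact tests for categorical ones, without assigning them to outcomes. Secondary outcomes are adjusted by Benjamini-Hochberg.

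**The concern.** An incidence outcome is a binary outcome, and under Data analysis it would be compared by a chi-square or exact test at each visit, without the baseline value. This uses only which side of 8 a patient is on.

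The therapy rule makes this awkward for depression. A patient must score at least 9 to be offered therapy, and a case is anyone at 8 or more, so all patients offered therapy start as depression cases. They affect the comparison only if they fall to 7 or lower. The severest patients, with the most room to improve, have the furthest to go before any gain registers. The same argument does not carry over fully to anxiety, because the trigger uses the depression subscale alone. There the loss is the ordinary one from cutting a score in two.

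At stake is whether a null secondary result on anxiety or depression could be read as evidence that the programme does not help.

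**Working it through.** **No plan figure to reproduce.** The 42 evaluable per arm in Sample size is for the EuroQol visual analogue scale. No power, mean, SD or case rate is given for HAD, so those inputs below are assumptions. Evaluable patients: 51 × 0.8 = 40.8, taken as 41 per arm (42 where stated). All tests are two-sided at 5%, before Benjamini-Hochberg.

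**Step 1: what the case rule registers for a patient offered therapy (entry score 9 to 21).**
- 21 to 8: gain of 13, still a case.
- 20 to 9: gain of 11, still a case.
- 9 to 7: gain of 2, no longer a case.

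**Step 2: closed-form check, same shift in every patient, 42 per arm.** The standardised shift with 80% power on the score is d = (1.960 + 0.842) × √(2/42) = 0.611. For a control case rate p1, the case rate under the shift is p2 = 1 − Φ(z(1−p1) + d). Power on case status is Φ((p1 − p2 − 1.96·SE0)/SE1), with SE0 from the pooled proportion and SE1 unpooled. For p1 = 40%:
- p2 = 1 − Φ(0.253 + 0.611) = 19.4%
- SE0 = √(2 × 0.297 × 0.703/42) = 0.0997
- SE1 = √((0.240 + 0.156)/42) = 0.0971
- power = Φ((0.206 − 0.195)/0.0971) = 55%

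| Control case rate | Case rate under shift | Power, case status | Per arm for 80% |
|---|---|---|---|
| 20% | 7.3% | 39% | 114 |
| 30% | 12.8% | 48% | 89 |
| 40% | 19.4% | 55% | 76 |
| 50% | 27.0% | 58% | 70 |

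**Step 3: simulation with baseline.** Baseline and 6-month scores are bivariate normal, rounded and truncated to 0 to 21, with SD 4 and 41 per arm. At a mean of 6.5, about 40% of controls are at 8 or more and about 31% exceed 8 at baseline.

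| Benefit | Correlation | Cut-off | t-test on score | Baseline-adjusted score |
|---|---|---|---|---|
| 2 points in all | 0.4–0.6 | 40% | 59% | 67–78% |
| 1 point in all, 3 more if above 8 | 0.4–0.6 | 42–48% | – | 61–73% |
| 3 points, only if above 8 | 0.5 | 16% | 20% | 22% |
| 4 points, only if above 8 | 0.5 | 23% | 31% | 32% |
| 5 points, only if above 8 | 0.5 | 30% | 42% | 44% |

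Repeat runs differ by one or two points; across them the last three rows span about 15–31% for the cut-off and 21–45% for the adjusted score. With control means of 5 and 8 and 2 points in all (correlation 0.5), the cut-off gives 35% and 46%, and the adjusted score 69% and 72%.

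**Step 4: why the gap shrinks when only patients above 8 benefit.** With 31% above 8, a 3- to 5-point gain averages 0.31 × 3 = 0.9 to 0.31 × 5 = 1.6 points over the arm, against 2 in the first row. Dilution and sample size then limit every method. A wider set (42 per arm, means 5 to 7, SD 4.5, correlation 0.6, gains of 3 to 6 points) gives 10–52% for the cut-off, 11–67% for the t-test and 12–71% for the adjusted score. The cut-off loses about 1 to 15 points against the t-test and 2 to 19 against the adjusted score.

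**Step 5: where the gain comes from.** For 2 points in all at correlation 0.5, power is about 41% (cut-off), 60% (t-test) and 71% (adjusted). About 19 points come from keeping the score and about 11 from using the baseline.

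**The case against.** Incidence is a legitimate question. It is the stated objective, the threshold is sourced, and a proportion is easy to explain. Education reaches the whole intervention arm, so preventing new cases among patients who start below 8 is a real aim that a case outcome captures. This stands, and it is why incidence should remain reported.

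The article also condenses a fuller plan. Data analysis lists tests for continuous variables, and a supplementary score analysis may exist elsewhere. This stands in part: nothing rules a score analysis out. But the outcome named and the rule fixed for HAD are binary, and a possible supplement does not change which comparison is tested.

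A reader might infer that the cut-off discards most of the effect in the treated patients, so that a working programme would be missed because of it. The figures do not support that. When benefit is confined to patients above 8, the adjusted score would usually miss it too.

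A reader might extend the point in full to PTSD. The article does not support that either. Its rule is a symptom-cluster algorithm, not a cut on the total; severity scores are mentioned as available; and baseline collection of the PCL-5 is only implied by the general description of the baseline visit. The lack of Spanish validation affects the total as much as the case rule, and no power figure here concerns the PCL-5.

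Benjamini-Hochberg applies equally to scores and is no argument against the cut-off.

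**Conclusion.** The point holds for the two HAD outcomes. The case rule registers a 2-point gain and can miss a 13-point gain in the patients selected for therapy, and a more powerful comparison is available from data already collected.

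The size depends on assumptions about HAD that the article does not supply. With a 2-point benefit in all patients, power rises from about 40% to 67–78%, part of it owed to baseline adjustment rather than to dropping the cut-off. With benefit only above 8 at baseline, it rises from about 15–31% to 21–45%. The adjusted score was ahead in every setting tried, but in the second case power stays low on either scale.

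For PTSD only the milder statement is supported: the named outcome is incidence, and no comparison of severity is specified beside it. These are secondary outcomes for which the trial was not sized, so the primary conclusion is unaffected.

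**What to change.** Before outcomes are compared by arm, state in the analysis plan that:
- the tested secondary comparisons for anxiety and depression are the between-arm differences in HAD anxiety and HAD depression score at 3 and 6 months, each adjusted for its own baseline value;
- the proportions at HAD 8 or more are still reported by arm at each visit, with a confidence interval for the difference, because incidence is the stated objective;
- the PCL-5 total is analysed beside the provisional PTSD diagnosis, adjusted for baseline if it was collected then, without a claim that the total is better validated, and with a statement of whether it enters the Benjamini-Hochberg set.

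For HAD, four score comparisons (two subscales, two visits) replace four incidence comparisons, so the adjusted set does not grow. Testing the PCL-5 total would add two.

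The cost is wording only: no new visits, questionnaires or patients. The downside is that a mean score difference is less direct to interpret than a proportion, which reporting both largely meets.

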### Statistical methods

#### Sample size

To calculate the sample size of the PAIN COVID clinical trial with an assumed average of 50 points on the visual analog scale of the EuroQOL-5D-5L for the control group, and a clinically relevant difference between the groups of 20%, for distribution of a tail with a type I error of 0.05 and a power of 80%, the sample size has been calculated as 84 patients, 42 for each arm. Assuming a loss to follow-up of 20%, the sample size needed is 102 patients (51 in each group).

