**Methods:**

The PAINCOVID trial is a unicentric randomized, controlled, patient-blinded superiority trial with two parallel groups. The primary endpoint is the health-related quality of life at 6 months after hospital discharge, and randomization will be performed with a 1:1 allocation ratio. This paper details the methodology and statistical analysis plan of the trial and was submitted before outcome data were available.

The estimated sample size is 84 patients, 42 for each arm. Assuming a lost to follow-up rate of 20%, a sample size of 102 patients is necessary (51 for each arm).

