### Data analysis

Qualitative variables will be presented as proportions, while for quantitative variables, the mean (standard deviation) or median (interquartile range), after checking for normality using the Shapiro-Wilk test, will be used. To compare variables across groups, Student *t* tests or Mann-Whitney *U* tests for continuous data and chi-square tests or exact tests for categorical variables will be carried out. Before parametric hypothesis testing, equality of variances will be studied using the Levene’s test, and if assumptions are not met, contrasts will be performed with the Welch’s test. An intention-to-treat approach will be followed. Two-tailed *P* values will be presented and a significance level of 0.05 will be used.

For the secondary outcomes, adjustment with the Benjamini-Hochberg procedure will be carried out.

A sub-analysis of the effect of treatment on compliers will be performed for the main outcome. Compliers are defined as those subjects that effectively receive the treatment they are allocated to. For the present study, compliers will be defined as individuals that, having been randomized to the intervention, complete at least two out of three medical visits and at least five out of seven psychological interventions. For the statistical analysis, instrumental variable analysis will be carried out. A two-sided probability (*p*) value of less than 0.05 will be considered to indicate statistical significance. The statistical analysis was performed using R (https://www.rstudio.com/) statistical software.

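### The sample size is worded for a one-tailed 5% test but the analysis is two-sided at 5%; taken as written, 42 per arm give about 70% power, not 80%

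*Protocol article*

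**What the plan says.** The Sample size section assumes "an assumed average of 50 points on the visual analog scale of the EuroQOL-5D-5L for the control group". It takes a 20% difference between the arms as clinically relevant. The calculation is made "for distribution of a tail with a type I error of 0.05 and a power of 80" per cent. The result it reports is that "the sample size has been calculated as 84 patients, 42 for each arm". Allowing for 20% loss, 102 patients (51 per arm) are to be enrolled. No standard deviation is given, and the section does not say whether 20% means 20% of 50 (10 points) or 20 points on the 0 to 100 scale.

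The Data analysis section sets the test: "Two-tailed *P* values will be presented and a significance level of 0.05 will be used". The paragraph on the complier analysis ends with "A two-sided probability (*p*) value of less than 0.05 will be considered to indicate statistical significance". No section provides a one-sided test of the primary outcome.

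The Methods part of the abstract repeats the number ("The estimated sample size is 84 patients, 42 for each arm") without sidedness or power.

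**The concern.** The test used to size the trial and the test used to analyse it differ. A one-tailed test at 0.05 has a critical value of 1.645 and a two-sided test at 0.05 has 1.960. A number of patients that just reaches 80% power against the first falls short of it against the second. If the one-tail wording describes what was done, the primary comparison has a risk of about 30%, not 20%, of missing the difference that the trial calls clinically relevant. A reader would then judge a non-significant result against a power that the planned test does not have.

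**Working it through.** **Inputs.** From Sample size: one tail, alpha 0.05, power 80%, 42 evaluable per arm, 20% loss, 51 enrolled per arm, control mean 50, difference 20%. From Data analysis: two-sided alpha 0.05. The SD is not stated. Normal quantiles: z(0.95) = 1.645, z(0.975) = 1.960, z(0.80) = 0.842.

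**1. Can 42 be reproduced?** No, because the SD is missing. One can only solve for the SD that would give 42, using SD = difference × √(42/2) / (z for alpha + z for power):

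| Sidedness of the calculation | 10-point difference | 20-point difference |
|---|---|---|
| One-sided 0.05 | 10 × 4.583 / 2.487 = 18.4 | 36.9 |
| Two-sided 0.05 | 10 × 4.583 / 2.802 = 16.4 | 32.7 |

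These SDs are back-calculated. None of them is an assumption that the protocol states.

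**2. Power of the planned test, taking the one-tail wording at its word.** If 42 per arm give 80% power one-sided at 0.05, the expected test statistic is 1.645 + 0.842 = 2.487. Against the two-sided critical value:

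power = Φ(2.487 − 1.960) = Φ(0.527) = 70%.

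The SD and the size of the difference cancel out, so this result depends neither on the missing SD nor on what 20% means. With the noncentral t distribution used for both steps, the figure is 69.8%.

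**3. Other numbers of evaluable patients.** The expected statistic scales with √(n/42).

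- 20% loss from 51: 51 × 0.8 = 40.8 per arm; 2.487 × √(40.8/42) = 2.451; Φ(2.451 − 1.960) = 69%.
- No loss: 51 per arm; 2.487 × √(51/42) = 2.740; Φ(2.740 − 1.960) = 78%.

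**4. Difference detectable at 80% power with 42 per arm.** The ratio to the planned difference is (1.960 + 0.842) / (1.645 + 0.842) = 2.802 / 2.487 = 1.127, so about 13% larger. If the planned difference is 10 points, that is about 11.3 points.

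**5. Number that would give 80% two-sided for the planned difference.** 42 × 1.127² = 53.3, so 54 evaluable per arm. This shows the size of the gap; it is not a recommendation.

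**The case against.** The strongest reply is that the one-tail phrase is awkward English and may be a slip, so the power could be right and the wording wrong. The figure of 42 does not settle it. By the t test, a two-sided calculation for 10 points with a round SD of 16 gives 42 per arm, and so does a one-sided calculation with a standardized difference of 0.55. This objection stands in part: the 70% figure is conditional on the text meaning what it says. It does not remove the point, because one-tailed is the natural reading, and under either reading one of the two sections needs correcting.

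It can also be said that the second two-sided statement closes the complier paragraph and may apply only there. That is fair, but the first statement is general and is enough.

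Loss could be below 20%. Even with no loss, two-sided power is about 78%.

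Nor is this a detail that an article leaves to a fuller document. The article states both sidedness choices, and they disagree.

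A reader might go further and infer that the SD was 18.4, that more patients must be recruited, or that adjusting for baseline would bring power back to 80%. The documents support none of these. The SD is a back-calculation that holds only for a one-sided calculation and a 10-point difference. Stating the power correctly needs no added patients. The gain from baseline adjustment depends on a correlation between baseline and 6-month scores that the protocol does not give.

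**Conclusion.** The contradiction over sidedness is certain. Its effect on power is conditional: if the calculation was one-sided as written, the planned two-sided test has about 70% power at 42 evaluable per arm (about 69% at 40.8, about 78% at 51), and the difference detectable at 80% power is about 13% larger than planned. These figures rest on accepting that 42 per arm give 80% power one-sided at 0.05; they do not depend on the SD. Only the conversion to 11.3 points depends on reading 20% as 10 points. If the calculation was in fact two-sided, the implied SD for 10 points is about 16.4, the stated 80% is right, and only the one-tail wording is wrong. A reader might infer that the trial is definitely underpowered; without the SD, the document cannot establish that.

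**What to change.** Keep the two-sided 0.05 test. In the Sample size section, state the SD, the difference in VAS points and the sidedness actually used in the calculation. The SD should be the sponsor's own value, not one worked back from 42.

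- If the calculation was one-sided, restate the power as about 70% for the two-sided test with 42 evaluable per arm, or give the larger difference detectable at 80% power (about 11.3 points if 10 was planned).
- If the calculation was two-sided, correct the one-tail wording and leave the 80%.

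Carry any changed figure into the abstract, which now gives only patient numbers. The cost is a few lines of text. No extra patients are needed; the downside, in the first case, is a less favourable stated power.

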## Methods

### Study design

The PAIN-COVID is a comparative, prospective, single-center randomized controlled trial that will include 102 patients (Fig. 1). The trial has been designed in accordance with the fundamental principles established in the Declaration of Helsinki, the Convention of the European Council relating to human rights and biomedicine, and the Universal Declaration of UNESCO on the human genome and human rights, and with the requirements established by Spanish legislation in the field of biomedical research, the protection of personal data, and bioethics, registered on May 9, 2020, at http://www.clinicaltrials.gov with identification No. (NCT04394169). Approval of the final protocol by the *Comité Ético de Investigación Clínica del Hospital Clínic de Barcelona*—approval number: HCB/2020/0549, Chairperson: [name] [name], on May 14, 2020.

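### The stated 102 randomized patients do not preserve 84 after a 20% loss; they cover a loss of at most 17.6%, at a cost of about one point of power

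*Protocol article*

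**What the plan says.** The Sample size section of the protocol article works in two steps. First, on the planning assumptions, "the sample size has been calculated as 84 patients, 42 for each arm". Second, the allowance for loss: "Assuming a loss to follow-up of 20%, the sample size needed is 102 patients (51 in each group". The Methods paragraph of the abstract gives the same second step: "Assuming a lost to follow-up rate of 20%, a sample size of 102 patients is necessary (51 for each arm". The Study design section takes the result as the enrolment target, describing a "single-center randomized controlled trial that will include 102 patients".

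The abstract also says that "randomization will be performed with a 1:1 allocation ratio", so the arms are meant to be equal. The article does not state the inflation formula and gives no other reason for 102.

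**The concern.** A sample size is inflated so that the required number of patients remains after the expected loss. The inflated figure can therefore be checked by taking the loss off again. Taking 20% off 102 does not return 84.

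The number 102 appears in the abstract, the Study design section and the Sample size section, and in the abstract and the Sample size section it is presented as what is needed at the plan's own loss rate. If it falls short, the 80% power statement does not hold under the conditions that the plan itself assumes. The Discussion also warns that limited mobility and pandemic restrictions may keep patients from visits, so the full 20% loss is a realistic case.

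**Working it through.** **Inputs**

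- Required evaluable: 84 in total, 42 per arm (Sample size).
- Loss to follow-up: 20% (Sample size; abstract, Methods).
- Stated number to randomize: 102 in total, 51 per arm (Sample size; abstract, Methods; total also in Study design).
- Allocation 1:1 (abstract, Methods).
- For the power step only: one tail, type I error 0.05, power 80%, control mean 50 points on the visual analog scale, difference 20% (Sample size).

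**Reproducing the plan's figure.** Multiplying on, n x (1 + d):

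- 42 x 1.2 = 50.4, rounded up to 51 per arm, which is 102 in total. This is an exact match.

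**Number that a 20% loss requires.** Dividing out, n / (1 - d):

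- In total: 84 / 0.8 = 105.
- Per arm: 42 / 0.8 = 52.5, rounded up to 53, which is 106 in total.
- Check: 105 x 0.8 = 84.

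This is 3 to 4 more than 102.

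**What 102 delivers**

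- After 20% loss: 102 x 0.8 = 81.6, so 81 to 82 patients (51 x 0.8 = 40.8 per arm).
- Shortfall against 84: 2 to 3 patients.
- Largest loss that still leaves 84: 1 - 84/102 = 18/102 = 17.6%.

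**Effect on power.** The article gives no SD, so two assumptions are needed: the 20% difference means 10 points (20% of 50), and the SD is the one that makes 42 per arm give exactly 80% power.

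- SD = 10 / (1.645 + 0.842) x sqrt(42/2) = about 18.4, one-sided.
- Power at 40.8 per arm = Phi(10 / (18.43 x sqrt(2/40.8)) - 1.645) = Phi(2.451 - 1.645) = 0.790.
- At 41 per arm it is 0.792, and at 40 per arm 0.783.

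If the SD is instead back-solved on a two-sided basis (about 16.4), power at 40.8 per arm is 0.789. On either basis the loss allowance costs about one percentage point.

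**The case against.** The strongest objection is that this hardly matters. The total of 105 is within 3% of 102, and the step to 106 comes only from rounding to equal arms. The 20% is itself a round planning guess, and the gap between 20% and 17.6% is smaller than the uncertainty in any such guess. All of this stands. It limits the weight of the point but does not make the sentence true.

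A second objection is that 102 would be right if the 20% were a share of the 84 completers (84 x 0.2 = 16.8, and 84 + 16.8 = 100.8, or 102 with equal arms). The article does not say so, and a loss to follow-up rate ordinarily means the share of randomized patients who are lost.

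A third is that multiplying on is not documented. That is correct: it is inferred from the exact match. The shortfall does not depend on it, because a 20% loss from 102 leaves fewer than 84 however 102 was reached.

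A reader might go further and infer that this error leaves the trial with power of only 68% to 69%, since the Data analysis section plans two-tailed tests. The documents do not support that reading. With an SD of 18.43, two-sided power is already about 70% with the full 42 per arm: Phi(2.487 - 1.960) = Phi(0.527). At 40.8 per arm it is Phi(2.451 - 1.960) = 0.688. Almost all of the drop from 80% therefore comes from sizing on one tail while testing on two. That is a separate issue and does not belong in the size of this one.

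**Conclusion.** The sample-size statement is wrong as written in the Sample size section and the abstract. The head counts (81 to 82 remaining, 17.6% covered, 105 or 106 needed) follow from the article's own numbers and need no outside figure.

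The consequence is minor. The fall in power to about 79% is conditional on the 10-point reading of the difference and on the back-solved SD. It would be too strong to conclude that the trial is materially underpowered for this reason or that it must enrol more patients.

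**What to change.** Leave enrolment at 102 and correct the statement in both places, the Sample size section and the Methods paragraph of the abstract. For example: 102 randomized patients (51 per arm) keep 84 evaluable patients for a loss to follow-up of up to 17.6%; with a loss of 20%, about 81 to 82 patients would be evaluable, and the power for that number is then given. In the Sample size section, state the SD and the difference in points on which that power rests, so that it can be checked.

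The cost is one sentence in each place and a slightly less favourable stated figure. Eligibility, endpoint, test and conduct are unaffected. Rewording is also the practical course, because the Trial status section anticipates the end of recruitment by September 25, 2020, before the article's publication date of 2021-07-24.
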